Secondary outcomes	Haemodynamics: TPR mPAP CO Cardiac index SV HR MRI parameters: RVEF RVESV RVEDV RVSV (volume) LVEF LVESV LVEDV LVSV flow Other parameters: 6MWT NTpro‐BNP WHO functional class Quality of life (EmPHasis‐10) Depression and anxiety symptoms (GAD‐2/7 and PHQ‐2/9) Medication compliance (PHoenix PRO questionnaire) Side effects	Confirm Rx: HR HR variability Cardiac rhythm Thoracic impedance Respiratory rate CardioMEMS: mPAP CO SV Smartwatch (Garmin Venu2): Physical activity Physiological measurements (TPR, mPAP, CO, cardiac index, SV, and HR) Phone apps: PRO (Phoenix remote questionnaire) Medication compliance (myCardioMems app) 6MWT

Abbreviations: 6MWT, 6‐min walk test; CO, cardiac output; GAD, Generalized Anxiety Disorder; HR, heart rate; LVEF, left ventricular ejection fraction; LVEDV, left ventricular end‐diastolic volume; LVESV, left ventricular end‐systolic volume; mPAP, mean pulmonary artery pressure; PHQ, Patient Health Questionnaire; PRO, patient‐reported outcome; RVEDV, right ventricular end‐diastolic volume; RVESV, right ventricular end‐systolic volume; RVSV, right ventricular stroke volume; SV, stroke volume; TPR, total peripheral resistance.

Established clinical study endpoint measures at maximal therapy will be compared to changes in remotely monitored parameters measured at 4 and 8 weeks to determine if the implanted devices can detect structured changes in the clinical therapy, thereby facilitating early assessment of clinical efficacy. Remotely monitored parameters to be correlated with maximal therapy assessments, measured as absolute change from baseline and area under the curve to 4 and 8 weeks on each therapy, include hemodynamics (mPAP, CO, cardiac index, TPR, day HR, night HR, and HR reserve), activity (minutes per day), 6MWT, and PRO.

The analysis will also be performed to determine if changes in established and remotely monitored parameters (primary and secondary endpoints) can detect individual patient‐level therapy effects, thereby determining the utility of remote monitoring for personalized treatment plans.

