**Figure 2 pul212337-fig-0002:**
[figure not shown]
Primary outcomes in landmark PAH randomized controlled trials with patient‐reported outcomes included as secondary endpoints. DFI, dyspnea fatigue index; EQ‐5D, EuroQoL five‐dimension; MLWH, Minnesota Living with Heart Failure questionnaire; M&M, morbidity and mortality; PAH, pulmonary arterial hypertension; PRO, patient‐reported outcome; PVR, pulmonary vascular resistance; SF‐36, Short‐Form 36; Exercise endpoint inclusive of 6‐min walk distance and actigraphy; ^a^Living with Pulmonary Hypertension (LPH) questionnaire was undertaken in PATENT‐1; however, this was considered exploratory.

Quality of life outcomes will be assessed weekly using the validated EmPHasis‐10 questionnaire.^34^ Validated questionnaires will be used twice monthly to screen for anxiety (GAD‐2)^35^ and depression (PHQ‐2) symptoms.^36^

Patients will also be asked to record, on a weekly basis, any side effects of the study medications and to track dose–response changes that are observed. Data will be collected on patients' attitudes toward their PAH medications and patient‐reported medication compliance (PHoenix PRO questionnaire; Supporting Information: Figure S1). All participants will be invited to co‐enroll in the COHORT‐digital study,^37^ which enables PRO reporting through a mobile application called Atom5™ (Figure 3). If participants decline to co‐enroll for digital PRO reporting, data for these outcomes will be collected using a 10‐item questionnaire via telephone communication into the eCRF.

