### Statistical analyses

#### Sample size calculation

The sample size was chosen to ensure adequate power to detect differences in the clinical efficacy of the two treatment approaches in population‐level analyses and to have adequate power to evaluate the ability of implantable/remote technology to provide early evaluation of such clinical efficacy. For comparing the clinical efficacy of the two treatment approaches, we have used published RVSV data reporting a minimal clinically important difference of 12 mL and within‐patient standard deviation (SD) of 16.5 mL.^38^ The current study will be powered using a standardized effect (SE) of 12/16.5 = 0.73. Assuming 1:1 randomization of the participants to the two treatment sequences, 40 participants will provide 90% power in the population‐level clinical efficacy analysis for a 5% two‐sided type‐I error rate, with SE of 0.73. This is below the SE previously reported for the pulmonary vascular resistance (PVR; SE = 353.4/219.0 = 1.61),^3^ and the RVEF (SE = 9.12/7.39 = 1.23)^20^ and comparable to that observed for the 6MWT (SE = 36.0/46.7 = 0.77).^6^ Therefore, the study will be well‐powered for population‐level analyses of these additional important outcomes.

The sample size of 40 also provides good power for assessing whether changes in remote physiological measures from baseline to 4 and 8 weeks (mPAP, CO, HR, and heart rhythm) are correlated with changes in clinical measures from baseline to 12 weeks. The sample size of 40 patients provides 90% power, at a two‐sided 5% type‐I error rate, for correlations greater than 0.5, which would represent those of clinical interest.

The study is not powered for formal mediation analysis, so this will be considered exploratory. No formal multiple‐testing correction will be applied.

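### The early-assessment correlations pair two changes from the same baseline time point, so for same-quantity pairs a shared baseline fluctuation gives a positive correlation without any drug response

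*Protocol article*

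**What the plan says.** Early assessment of efficacy by remote monitoring is one of the two main aims (Protocol article, Objectives and endpoints). That section states: "Established clinical study endpoint measures at maximal therapy will be compared to changes in remotely monitored parameters measured at 4 and 8 weeks". It lists the remote correlates as mPAP, CO, cardiac index, TPR, day and night HR, HR reserve, activity, 6MWT and PRO, each summarised as absolute change from baseline and as area under the curve to Weeks 4 and 8.

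The Sample size calculation section makes this a change-against-change analysis. On the early side it takes the remote changes to Weeks 4 and 8 in mPAP, CO, HR and heart rhythm. On the late side it asks whether they "are correlated with changes in clinical measures from baseline to 12 weeks". Its power claim reads: "The sample size of 40 patients provides 90% power". The test is two-sided at the 5% level, and the target is worded as follows: "for correlations greater than 0.5, which would represent those of clinical interest".

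The Statistical analysis plan section tests for a significant correlation and names one Week 12 outcome, MRI RVSV (flow). It gives no null value other than zero and no handling of baseline for the correlations, although the primary efficacy model does adjust for within-period baseline.

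Table 1 lists mPAP, CO, SV, HR and 6MWT in both the hospital and the remote columns, and cardiac index and TPR also appear on both sides. EmPHasis-10 stands in the hospital column, but the Patient-reported outcomes section has it completed every week: "Quality of life outcomes will be assessed weekly using the validated". The remote PRO in Table 1 is the Phoenix questionnaire.

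**The concern.** Both change scores start from the patient's state at the same time point. If a patient's mPAP is high, or the walk poor, by chance around baseline, and both the remote and the clinic measurement see it, the patient appears to improve by Week 4 and again by Week 12. The two changes then correlate although the drug did nothing. Zero is therefore the wrong reference for such pairs, and a value near 0.5 need not mean early detection of efficacy.

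The bias runs towards the hoped-for answer on a main aim. It is separate from multiplicity, since one pre-named correlation would be affected just as much, and more patients would only make the false result more certain.

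**Working it through.** **Inputs from the article:** n = 40, two-sided 5%, correlation of interest 0.5, stated power 90%. **Not in the article, so assumed:** equal, independent within-patient variance v at each visit, no drug response, and a share L (0 to 1) of the visit fluctuation that both measurements see.

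**1. The plan's own figure.** Fisher z: power = Φ(atanh(0.5)·√(40−3) − 1.96) = Φ(0.5493 × 6.083 − 1.96) = Φ(1.38) ≈ 91.6%. This agrees with the stated 90%. The test against zero is significant when |r| exceeds 0.312.

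**2. Null correlation.** Let X = remote Week 4/8 minus remote baseline, and Y = clinic Week 12 minus clinic baseline. With no response, the only shared term is the common part of the baseline fluctuation:
- Cov(X, Y) = L·v
- Var(X) = Var(Y) = 2v
- corr(X, Y) = L·v / 2v = L/2

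**3. Consequence at n = 40** (simulation, 20,000 trials per row):

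| L | Null correlation | Significant against zero | Observed r > 0.5 |
|---|---|---|---|
| 0 | 0 | 5% | about 0% |
| 0.25 | 0.125 | 12% | 0.5% |
| 0.5 | 0.25 | 34% | 4% |
| 0.75 | 0.375 | 68% | 18% |
| 1 | 0.50 | 92% | 52% |

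Fisher z gives nearly the same significance rates, for example 34.2% at L = 0.5.

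**4. 0.5 is not a ceiling.** If one baseline reading enters both changes, the correlation is v0/√((v0+v4)(v0+v12)), where v0, v4 and v12 are the visit variances. With v4 half of v0 it is 1/√(1.5 × 2) = 0.58. With both follow-up variances half of v0 it is 1/1.5 = 0.67.

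**5. Averaging helps but does not remove it.** Suppose the remote baseline and the remote follow-up are both 7-day means, the baseline mean includes the clinic day, and daily fluctuation is fully shared. Then Cov = v/7, Var(X) = 2v/7 and Var(Y) = 2v, so r = (1/7)/√(4/7) = 0.19, significant about 22% of the time.

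**6. Splitting removes it under these assumptions.** With the clinic day left out of the remote mean, the simulated mean correlation is 0.00 and the significance rate about 5%.

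**7. Baseline as a covariate does not do the same.** If readings of one patient correlate ρ between visits, the partial correlation of Week 4 with Week 12 given baseline is (ρ − ρ²)/(1 − ρ²) = ρ/(1 + ρ). With no response this is 0.33 at an assumed ρ = 0.5 and 0.44 at ρ = 0.8.

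**The case against.** A reader might infer that both changes subtract one and the same reading, so that a null correlation of 0.5 and a 92% false-positive rate are what the plan will produce. The article does not support that. Table 1 lists hospital and remote measures separately, independent instrument errors do not couple, and L appears nowhere. The 0.5 belongs to L = 1 with equal variances. A multi-day remote baseline, which the article neither states nor excludes, already brings it down to about 0.19.

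Three further points against the concern are fair:
- The only Week 12 outcome named in the analysis section is MRI RVSV (flow), a different instrument and mostly a different quantity from the remote parameters. Coupling there is weakest and comes mainly through remote SV and CO. Same-quantity pairs enter through the general reference to clinical measures in the sample size section and the list under Objectives and endpoints.
- EmPHasis-10 is never named as the remote correlate, and the 0.5 threshold is attached to mPAP, CO, HR and heart rhythm, not to PRO or 6MWT. Weekly collection makes the same-instrument case possible, not planned.
- An area under the curve of raw values subtracts no baseline, and the remote HR summaries (day, night, reserve) are not identical to hospital HR.

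It can also be said that the baseline window is a derivation rule for the statistical analysis plan. That does not dispose of the point. The article itself fixes change against change, a significance test and a threshold, and following those as written biases same-quantity pairs upwards for any L above zero.

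**Conclusion.** The concern holds for pairs that measure the same or a closely related quantity: mPAP, CO/SV, cardiac index, TPR, HR, 6MWT, and a PRO if one instrument is used on both sides. For these, zero is not the correlation expected without drug response. The size cannot be read from the article. It runs from no inflation (5%) at L = 0 through 12% and 34% at L = 0.25 and 0.5 to 92% at L = 1, assuming equal and independent visit variances. Unequal variances can take the null correlation above 0.5. The RVSV (flow) analysis is affected least. The change should be made, because it bears on a main aim and costs little.

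**What to change.** For these correlations, in each treatment period:
- Define the remote baseline as the mean of several pre-drug readings that exclude the day of the clinic baseline.
- Use the clinic-day value only for the Week 12 clinical change.
- Compute the area under the curve as change from that separate remote baseline.
- Where one instrument supplies both sides and its baselines cannot be split, do not count the correlation as evidence of early assessment.

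Baseline as a covariate is not a substitute, because visits of the same patient stay correlated after adjustment for one noisy baseline (step 7).

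The cost is endpoint-definition wording. The Discussion says device data are relayed daily, and EmPHasis-10 is weekly, so no new procedure should be needed for these. The downsides are a slightly noisier baseline where few pre-drug readings exist, as may be so for the home walk or a PRO, and that a fluctuation lasting several days is only partly removed.

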### Study population

The study aims to recruit 40 patients with PAH, established on PDE5i and ERA, through the UK National Pulmonary Hypertension Clinical Studies Network (UNIPHY)—a collaboration of UK centers commissioned for the treatment of PAH, providing access to all patients within the UK currently receiving targeted therapy for PAH (>5000).^32^, ^33^ Suitable patients will be identified from existing patient lists by local teams and invited to screening via clinical and research teams.

Eligible patients meeting the inclusion and exclusion criteria (Table 2) will be established on PDE5i/ERA dual therapy and will meet NHS England's National Commissioning and ESC guideline criteria for initiation of IP receptor agonist or sGCS.^2^, ^9^, ^10^ While it is expected the majority of patients recruited will have intermediate‐low risk PAH, patients with intermediate‐high risk PAH who decline intravenous therapy will also be considered.

**Table 2 pul212337-tbl-0002:** Summary of eligibility criteria.

**Inclusion criteria:** 1. Able to provide informed consent 2. Age 18–80 years 3. PAH which is idiopathic, heritable, or associated with drugs, toxins, or connective tissue disease 4. Stable PAH therapeutic regime comprising any combination of ERA and PDE5i for at least 1 month before screening (unless unable to tolerate therapy) 5. WHO functional class III 6. Resting mPAP ≥20 mmHg, pulmonary capillary wedge pressure ≤15 mmHg, pulmonary vascular resistance ≥2 Wood Units measured by right heart catheterization at time of diagnosis 7. 6MWT > 50 min at entry 8. eGFR > 30 mL/min/1.73 m² at entry 9. Inadequate treatment response (clinically determined)
**Exclusion criteria:** 1. Unable to provide informed consent 2. Pregnancy 3. Unprovoked pulmonary embolism (at any time) 4. Acute infection at time of screening (rescreening is permitted) 5. PAH due to human immunodeficiency virus, portal hypertension, schistosomiasis, congenital heart disease 6. Pulmonary hypertension due to left heart, lung, thromboembolic, or unclear/multifactorial disease (Groups II–V) 7. Unable to tolerate aspirin or P2Y12 inhibitor 8. Hypersensitivity to selexipag or riociguat 9. Clinically significant renal disease (eGFR ≤ 30 mL/min/1.73 m^2^) 10. Anemia (hemoglobin <10 g/dL) 11. Left‐sided heart disease and/or clinically significant cardiac disease, including but not limited to any of the following: aortic or mitral valve disease greater than mild aortic insufficiency; mild aortic stenosis; mild mitral stenosis; or moderate mitral regurgitation

Abbreviations: eGFR, estimated glomerular filtration rate; ERA, endothelin‐1 receptor antagonist; mPAP, mean pulmonary artery pressure; PAH, pulmonary arterial hypertension; PDE5i, phosphodiesterase‐5 inhibitor.

### Device implantation

Eligible patients will be implanted with CardioMEMS and Confirm Rx ICM devices using standard techniques and remote monitoring data collected using regulatory‐approved online portals.^28^

### Treatment

Patients will be randomized 1:1 to one of two treatment sequences (Figure 1), with comparisons to be made using patient‐level data within the two treatment arms. Randomization will be done by authorized staff at study sites using a concealed randomization system via the Zeesta electronic case report form (eCRF—www.zeesta.ai/) portal. A block randomization stratified by site with a block size of four will be employed.

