CardioMEMS™ HF System (Abbott) is a wireless, PAP monitor implanted at the time of right heart catheterization to provide remote measurement of cardiopulmonary hemodynamics. CardioMEMS is approved for routine clinical practice in the USA and Europe, and to date over 30,000 of these monitors have been implanted. The Confirm Rx™ ICM (Abbott) is a minimally invasive regulatory‐approved cardiac monitor, implanted in a clinical setting for patients who experience unexplained symptoms, such as dizziness; palpitations, chest pain, syncope, shortness of breath, as well as for patients who are at risk for cardiac arrhythmias. Over 40,000 Confirm RX™ have been implanted and the device is in routine clinical use in the United Kingdom.

Here, we detail the protocol for a study in which patients with PAH, established on guideline‐recommended dual oral therapy and evaluated as intermediate‐low risk,^29^ will be implanted with CardioMEMS and ICM devices. Following implantation, patients will enter a 2 × 2 crossover study in which PDEi will be replaced with sGCS (ERA + sGCS), or an IP receptor agonist will be added to PDEi and ERA (PDEi + ERA + IP receptor agonist). Data obtained from remote monitoring will be compared with that from established clinical investigations undertaken at baseline and maximal therapy on each drug. The crossover design of this study, which will incorporate structured up‐titration of these drugs, is aimed at evaluating the capacity of implantable technology for early evaluation of the clinical efficacy of these drugs. A crossover study is a logical study designed to investigate the intra‐patient efficacy of these treatment options and increase the power to detect clinical efficacy. Additionally, the study will provide insight into the capacity of remote monitoring technology to facilitate trials that are not currently possible due to the requirement for repeated, hospital‐based invasive/imaging procedures.

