## METHODS

### Study design

This open‐label, phase 4, multicentre, randomized 2 × 2 crossover study (NCT05825417) in patients with PAH established on dual therapy (PDE5i/ERA) will evaluate the effects via clinical investigations, patient‐reported outcomes and remote cardiac monitoring of two therapeutic strategies—adding an oral drug targeting the prostacyclin pathway (selexipag; PDEi + ERA + IP receptor agonist) and switching of PDE5i to an sGCS (riociguat; ERA + sGCS). Using the 2 × 2 crossover trial design, patients will receive both therapies, but the sequence will be randomly assigned with washout phases between therapies, and assessments of response to each therapy to be performed.^30^ The study protocol was approved by the NHS Health Research Authority (IRAS PROJECT ID 325120, REC Reference 23/NE/0067). A tabulated summary of all visits and assessments is provided in Supporting Information: Table S1.

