### Clinical assessments

Patients will undergo clinical assessments at baseline before receiving study drug treatment, and at Weeks 12 and 27 of the treatment schedule (Figure 1); these will include hemodynamics, 6MWT, MRI, and NT‐proBNP assessments.

MRI analysis will be provided by a study‐appointed core lab using certified clinicians; scans will be deidentified and analyzed in random order independent of patient and time point. Analysis of primary and secondary endpoints will be undertaken in a blinded manner by an independent statistical team in accordance with a pre‐specified statistical analysis plan.

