## DISCUSSION

Patients with PAH receiving dual combination treatment (PDE5i + ERA) who are stratified as being at intermediate‐low risk^39^ are recommended to intensify therapy via the addition of the IP receptor agonist, selexipag, or to switch from a PDE5i to the sGCS, riociguat.^9^, ^10^, ^29^ There is clinical equipoise between triple therapy with selexipag + PDE5i + ERA and dual therapy with riociguat + ERA. Conducting head‐to‐head clinical trials to compare treatment strategies in patients with PAH is challenging due to the current necessity for repeated, hospital‐based invasive/imaging procedures to evaluate treatment efficacy. Remote hemodynamic and cardiac monitoring may provide a means for early, minimally invasive evaluation of clinical efficacy and early identification of clinical worsening in patients with PAH, which may facilitate study designs evaluating dose–response, time‐to‐effect and head‐to‐head comparison. This study is designed to assess the individualized effect of selexipag and riociguat on RV stroke volume as measured by cardiac MRI, and to determine whether remote monitoring devices can be used to provide an early assessment of the clinical efficacy of drug therapies for PAH. This hybrid drug‐device regulatory‐approved design represents the first evaluation of an sGCS and IP agonist.

This blinded analysis of objective MRI measures provides an efficient, robust, and effective clinical study structure. As the primary endpoint is objective with blinded analysis, patients and clinicians will not be blinded to the sequence of drug allocation and up‐titration.

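### A single, published block size of four within site, in an open-label trial randomised by site staff, lets up to one third of sequence allocations be deduced before randomisation and so weakens concealment

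*Protocol article*

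**What the plan says.** The Treatment section of the protocol article sets out the allocation. The ratio and the unit of randomisation are clear: "Patients will be randomized 1:1 to one of two treatment sequences". The same section says who does it and how: "Randomization will be done by authorized staff at study sites using a concealed randomization system via the Zeesta electronic case report form" portal. It then fixes the restriction: "A block randomization stratified by site with a block size of four will be employed". No variation in block size is mentioned.

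The trial is open-label (Study design), and the Discussion confirms that "patients and clinicians will not be blinded to the sequence of drug allocation". Under Study population, local teams identify suitable patients from their own lists, and clinical and research teams invite them to screening.

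Three other statements bear on the consequences:

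- Only the order of treatment is random: "patients will receive both therapies, but the sequence will be randomly assigned" (Study design).
- The primary measure is read blind by a core laboratory: "scans will be deidentified and analyzed in random order independent of patient and time point" (Clinical assessments).
- The primary model analyses change from baseline to 12 weeks, both taken within the treatment period, with a fixed period effect. A participant may contribute one or two observations (Statistical analysis plan section).

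**The concern.** Concealment is meant to stop those who put a patient forward from knowing what that patient will get. A central system hides the list, but it cannot hide what follows from the history. Here the block size is constant, it is in print, it applies within site, and each earlier patient's sequence is visible at that site. The remaining slots of a block can then be worked out.

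Foreknowledge matters if staff prefer one order for some patients. The two orders do differ at the start: one begins by adding selexipag, the other with a PDE5i washout. There is some room over timing, since inadequate response is clinically determined and rescreening after acute infection is allowed. If patients of different kinds were steered to different sequences, the sequence groups would no longer be comparable. That could reach the drug contrast through patients lost before the second period, or through differences in how response changes from the first period to the second.

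**Working it through.** **Inputs.** Block size 4, ratio 1:1, stratified by site (Treatment); sequence unblinded (Discussion); 40 patients (Study population). The number of sites is not given, so it is varied below as an assumption.

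**The plan's own figure.** The article gives no figure for predictability. Its sample size does reproduce: N = 2 × (1.960 + 1.282)² × (16.5/12)² = 39.7, rounded up to 40, with 90.2% power by the normal approximation. Neither the present block rule nor the proposed one enters that formula.

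**Share of allocations that are certain.** Call the sequences A and B. An allocation is certain once one sequence has been used twice in the block. The six possible blocks give:

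| Block | Certain allocations |
|---|---|
| AABB | 2 |
| ABAB | 1 |
| ABBA | 1 |
| BAAB | 1 |
| BABA | 1 |
| BBAA | 2 |
| Total | 8 of 24 = 33.3% |

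By position, the probability of certainty is 0, 0, 1/3 and 1, which sums to 1.33 of 4. For 40 patients in complete blocks this is 40/3, or about 13.

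**Best-guess success.** The observer always guesses the sequence used less often so far. Expected correct guesses per block are 0.5 + 0.667 + 0.667 + 1 = 2.83 of 4, or 70.8%, against 50% without the blocks.

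**Incomplete last blocks.** One third is the highest expected share, because an unfinished block stops before its most predictable slots. Applying the position probabilities to 40 patients spread at random over sites gives:

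| Sites (assumed) | Expected share certain |
|---|---|
| 2 | 31% |
| 5 | 28% |
| 8 | 25% |
| 10 | 23% |
| 15 | 17% |
| 20 | 12% |

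Equal site sizes give other values: 33% for 5 sites of 8, 27% for 8 sites of 5, and 0% for 20 sites of 2.

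**What reaches the drug contrast.** Let C1 and C2 be a patient's change over each 12-week period from that period's own baseline. For patients with both periods, and leaving aside the baseline covariate, the estimated drug difference is half the difference between the sequence groups in mean (C1 − C2). A patient who declines steadily loses about the same amount in each period, so the decline cancels in C1 − C2. Steering causes bias only if the steered patients differ in how their 12-week change shifts from period 1 to period 2. The common period effect does not remove such a difference. Patients with one period have no C1 − C2; they enter through between-patient information, where steering acts directly.

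**Effect of varying the block size.** This was simulated for an observer who knows the set of sizes and the full site history, with 4 to 40 patients per site:

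| Block sizes | Certain | Best-guess success |
|---|---|---|
| 4 only | 33% | 71% |
| 2, 4 | 8-11% | 71-72% |
| 4, 6 | 1-6% | 66-69% |
| 2, 4, 6 | 1-4% | 66-70% |

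**The case against.** The strongest reply is that the plan already specifies concealment and that the design blunts the consequences. Much of this stands.

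- The randomisation system is described as concealed and runs through the eCRF portal. The list stays hidden, and at least two thirds of allocations in expectation are not certain in advance. A reader might infer that concealment fails altogether; the article does not support that.
- A reader might also take one third as the expected figure and place the foreknowledge before enrolment. One third needs complete blocks and staff who know the block size and track every earlier allocation. Devices are implanted before patients enter the crossover (Introduction), and the article does not say when randomisation falls relative to enrolment. Only foreknowledge before randomisation can be claimed.
- Every patient is to receive both strategies and the plan asserts equipoise between them, so the motive to steer is weak. The article does not say that those who invite patients are the same people who randomise them.
- Blinded MRI reading guards against biased measurement. It does not affect who enters which sequence, so it is only a partial answer.
- A reader might attach a bias in millilitres. If the between-period shift differed by s mL between patient types and every predictable slot were steered, sequence means would differ by s/3 and the contrast by s/6. An s of 6 to 12 mL would give 1 to 2 mL. But s has no source in the article, perfect steering at every site is an extreme assumption, and the formula does not cover patients with one period. That figure should not be used.

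What the reply does not remove is the deduction itself. It follows from the stated rule and the open history, whatever the portal hides.

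**Conclusion.** The point holds as a modest weakness in a stated design choice. Up to one third of sequence allocations can be deduced before randomisation: 33% in complete blocks, about 23% to 31% with random spread over 10 down to 2 sites, and less with more sites. This assumes that site staff know the published block size and keep track of earlier allocations.

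The likely bias in the primary contrast is small, and its size cannot be derived from the article. It would come mainly from patients who contribute one period only, or whose response shifts between periods. No dropout rate and no preferred order is documented.

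The judgement that bias is small relies on the within-period baseline named in the Statistical analysis plan section. Clinical assessments names MRI at baseline and at Weeks 12 and 27 only, and the visit schedule (Figure 1, Table S1) is not shown, so this reading follows the stated analysis.

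**What to change.** Replace the fixed block of four with randomly varying block sizes within site, for example 2, 4 and 6. Keep the sizes from the sites. If recruitment has begun, apply the change to all blocks not yet opened. Sizes 2 and 4 alone do less, as the last table shows.

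The gain should be stated fairly: certain predictions fall from 33% to about 1-4%, but best-guess success falls only from 71% to about 66-70%. The benefit is the removal of certainty, not of all predictability.

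The cost is a setting in the randomisation system and one sentence in the protocol. Sequences at a site may be out of balance by one or two patients. The largest possible imbalance is half the largest block, so it rises from 4/2 = 2 to 6/2 = 3. The planned total of 40 does not change.
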